## Methods/design

This pilot prospective cohort trial will utilize a concurrent mixed-methods design to obtain information about intervention feasibility, acceptability, and sustainability and assess preliminary evidence of improved outcomes.

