**Fig. 1 Fig1:**
[figure not shown]
Adapting the CenteringPregnancy model for uterine fibroids

Healthcare advocates from TWDP co-facilitate each session to aid in maintaining a patient-centered experience.

CPWF cohorts are implemented using a hybrid modality, with the first and last sessions conducted in person, and the remaining sessions conducted via Zoom (Fig. 1). A total of 7 cohorts will receive the program at BMC, and a total of 6 cohorts will receive the program at Emory/Grady. All CPWF participants complete a “Dear Fibroids” letter to their fibroids at the beginning of the session, a personal effort to define and process how fibroids have impacted their daily lives. We utilize Zoom features such as breakout rooms, screen sharing, and polls for greater engagement in the virtual space. For example, one strategy for online engagement includes activities to establish rapport between patients via Zoom breakout rooms, focused on discussing fibroid experiences, unique or fun facts about participants, and hobbies. Other strategies include mindfulness activities, “ball toss” activities to reinforce learning in a playful way, and artistic exercises such as drawing in the “Past, Present and Future” exercise in which participants color a tree with branches symbolizing various stages in their fibroid journey.

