**Fig. 2 Fig2:**
[figure not shown]
Centering Patients with Fibroids (CPWF) recruitment and participation flow

In addition to these screening and recruitment practices, we used EPIC/MyChart to reach patients not seen in the OB/GYN practice who are diagnosed with UF. We obtained a list of non-pregnant patients with fibroid diagnoses as a preliminary eligibility screening, then sent a study recruitment letter with Opt Out language to the patient’s MyChart inbox. We posted digital flyers with QR codes on waiting room television monitors in clinics throughout the hospital to supplement paper recruitment flyers. We reached out to the Family Medicine and General Internal Medicine departments at BMC and Emory/Grady to identify provider research champions to assist us in identifying potentially eligible patients/connecting them with the study opportunity through MyChart. Finally, we will access emergency department and gynecology follow up referral lists to screen patients for CPWF and reach out to potentially eligible subjects. Participants will be remunerated up to $200 via reloadable gift cards called “ClinCards” for survey completion, lab draw, and session attendance. We emphasize that CPWF is a program designed to complement, rather than replace, one-to-one gynecological care with a participant’s provider.

In addition to recruiting patients, we recruited healthcare leaders and providers at Boston Medical Center, Emory University Hospital Midtown, and Grady Memorial Hospital to participate in interviews. We will identify those who are invested in improving access to quality care and health outcomes for patients seeking care at BMC, Emory University Hospital Midtown, and Grady Memorial Hospital. Interviewees will be leaders and providers who have had some level of contact with the Fibroid Center, Emory University Hospital Midtown, and Grady Memorial Hospital or provide care to women seeking care related to symptomatic uterine fibroids. They are contacted via email and asked to participate. If they agree, we will obtain consent and schedule interviews.

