### Quantitative methods

To assess preliminary program impact on physical and mental health outcomes, participants will complete self-reported surveys during their participation in this study: pretest, posttest, and 3 month follow up. The surveys will include demographic questions and a series of validated measures, including the Uterine Fibroid Symptom and Quality of Life (UFS-QOL), the Everyday Discrimination Scale, Patient Health Questionnaire-9 (PHQ-9), and the Instrument for Evaluation of the Experience of Chronic Patients (IEXPAC).

As the aim of this pilot study is to assess preliminary outcomes as well as feasibility, acceptability, and sustainability, achieving a predetermined sample size for power was not necessary. We anticipate 10-12 participants per cohort for a total of 13 cohorts, 7 at BMC and 6 at Emory/Grady. As such, we will perform comparison of mean scores of the various validated survey instruments using analysis of variance (ANOVA) tests. We will also ask participants to give blood for serum studies including complete blood count (CBC), Anti-Müllerian hormone (AMH), and 25-OH-Vitamin D. Values will be compared at baseline and 3 months after the program completion. We hypothesize decreased anemia and vitamin D deficiency among program participants at 3 month follow up, and variable change in the AMH level related to the age at the time of program participation.

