Our study group will describe the experiences of participants and feedback from providers and other healthcare leadership on program implementation and will identify modifiable intervention targets and organizational, provider, and patient level factors associated with successful implementation of CPWF. Quantitative data include survey results and serial lab values for hemoglobin, hematocrit, vitamin D, iron studies, and AMH. Hemoglobin and hematocrit are markers of anemia, which is prevalent in patients with heavy menstrual bleeding due to UF [30]. Vitamin D deficiency is a possible risk factor for UF occurrence. Vitamin D concentrations have been found to be inversely associated with uterine fibroid prevalence, especially in Black women [31]. AMH is used as a marker of functional ovarian reserve [32] and is thus valuable in counseling women about reproductive and treatment planning in the setting of gynecological conditions such as UF [33]. The combination of both qualitative and quantitative methods will allow us to capture the benefits of CPWF over a shorter timeframe and to lay the groundwork for larger studies. We will use the data from our mixed methods study to direct next steps, including future iterations of the curriculum in response to feedback from participants, faculty, clinicians, and other key stakeholders, and a larger multisite randomized controlled trial to further explore the efficacy and generalizability of CPWF across the country.

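### Uncontrolled baseline-to-follow-up change is presented as programme impact, although season, continuing gynaecological care and (for survey scores) regression to the mean can move the same outcomes

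*Protocol article*

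**What the plan says.** The Methods/design section describes a single-group study: "This pilot prospective cohort trial will utilize a concurrent mixed-methods design". Under Intervention, all cohorts are treated: "A total of 7 cohorts will receive the program at BMC, and a total of 6 cohorts will receive the program at Emory/Grady". No usual-care or waiting group is described.

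Quantitative methods opens with the purpose "To assess preliminary program impact on physical and mental health outcomes". For the blood tests the stated analysis is "Values will be compared at baseline and 3 months after the program completion", followed by the directional hypothesis "We hypothesize decreased anemia and vitamin D deficiency among program participants at 3 month follow up". Survey means are to be compared by ANOVA. No covariate is named for either.

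Recruitment says that "CPWF is a program designed to complement, rather than replace, one-to-one gynecological care", so usual treatment runs alongside the programme. Entry requires symptomatic fibroids (Intervention), and emergency department and gynaecology follow-up lists are among the recruitment sources (Recruitment). The Discussion says that combining qualitative and quantitative methods "will allow us to capture the benefits of CPWF over a shorter timeframe". It leaves efficacy to a later randomised trial.

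**The concern.** A before-after difference in one group estimates the programme effect only if nothing else would have moved the outcome between the two visits. The article itself points to three things that could:

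- **Season.** The two draws fall at different times of year, and vitamin D is one of the two blood outcomes with a directional hypothesis. Members of a cohort start together, so they share the same seasonal shift.
- **Concurrent care.** Procedures, hormonal therapy, iron or vitamin D prescriptions and transfusions between visits can change haemoglobin, vitamin D, AMH or UFS-QOL. Some of that care would have happened without the programme.
- **Regression to the mean.** People enrolled while symptomatic may score worse at entry than they do on average. This concerns the survey scores. Entry is not selected on haemoglobin or vitamin D.

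Followed as written, the plan could report spring sunlight, ordinary treatment or symptom fluctuation as programme impact. The Discussion says these data will direct next steps, including the curriculum and a larger trial.

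**Working it through.** The article states no alpha, power, SD or effect size, so there is no power figure to reproduce. Its own cohort arithmetic holds: 7 + 6 = 13 cohorts, and 13 × 10 to 13 × 12 = 130 to 156 participants, with midpoint 13 × 11 = 143. All drift, correlation, SD and amplitude values below are assumptions.

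**1. Interval between draws.** 8 weeks (Intervention) + 3 months, about 13 weeks (Quantitative methods) = about 21 weeks, or 4.8 months.

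**2. Chance of a significant improvement with zero programme effect.** In baseline SD units, the standard error of the mean paired change is √(2(1 − r)/N). For drift d, the approximate chance of a significant improvement (two-sided 5% test) is Φ(d/SE − 1.96). For example, with r = 0.8 and N = 143, SE = √(0.4/143) = 0.053. Then d = 0.10 gives Φ(1.89 − 1.96) = 0.47, and d = 0.20 gives Φ(3.78 − 1.96) = 0.97. The rows for N = 130 and N = 91 use the noncentral t.

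| N | r | d = 0 | d = 0.1 SD | d = 0.2 SD |
|---|---|---|---|---|
| 143 | 0.8 | 2.5% | 47% | 97% |
| 130 | 0.7 | 2.5% | 31% | 83% |
| 130 | 0.5 | 2.5% | 20% | 62% |
| 91 (30% loss) | 0.7 | 2.5% | 23% | 68% |
| 91 (30% loss) | 0.5 | 2.5% | 16% | 47% |

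**3. Where such a drift could come from in survey scores.** Regression to the mean is (1 − r) × the entry deviation from the reference mean. With r = 0.8 and entrants 0.5 to 1.0 SD worse than that mean, it is 0.2 × 0.5 = 0.10 to 0.2 × 1.0 = 0.20 SD.

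**4. Season and vitamin D.** For a yearly sine wave, the largest difference between draws 21 weeks apart, as a share of the peak-to-trough swing, is sin(π × 21/52) = 0.955. Sign and size depend on start dates. Assume amplitude 2 to 4 ng/mL, SD 10 ng/mL, r = 0.7, a peak at the start of September and N = 130:

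| Cohort starts | Mean seasonal drift (ng/mL) | Chance of significant improvement |
|---|---|---|
| February to April | +3.4 to +6.9 | over 99% |
| Evenly over the year | 0 | 2.5% |
| 13 random dates | varies around 0 | 10% to 21% |
| September to November | −3.1 to −6.1 | about 0% |

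In the last row season would hide a real improvement. The article gives no cohort calendar, so no row can be singled out.

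**5. Concurrent care and anaemia.** Assume 40% to 50% anaemic at baseline, 20% to 40% of these resolving under usual care, and 5% to 10% of the others becoming anaemic. With 130 participants, a simulated exact McNemar test shows a significant fall in 6% to 99% of studies with no programme effect. At the low end, expected resolutions are 0.40 × 0.20 = 8% of participants against 0.60 × 0.10 = 6% new cases. At the high end they are 0.50 × 0.40 = 20% against 0.50 × 0.05 = 2.5%.

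**The case against.** Several points on the other side stand.

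- The article calls the study a pilot and its evidence preliminary, and leaves efficacy to a randomised trial. A single-arm pilot is a legitimate choice. The sentence about benefits also concerns the combined qualitative and quantitative work, not laboratory change alone.
- The article names no test for the blood values and does not rule out covariates. The full protocol or analysis plan, not shown, may contain seasonal terms or treatment recording. The point therefore rests on the stated attribution, not on that silence.
- Recruitment is broad. It includes MyChart letters to patients not seen in gynaecology, flyers and primary-care contacts, and qualifying imaging may be up to 12 months old. Enrolment at a symptom peak is plausible for some participants, not established for all.

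Stronger readings that a reader might infer are not supported:

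- *Season favours the programme.* It can act in either direction and cancels if starts are balanced over the year. Cohorts have run in sequence since 2022, which makes one common start season unlikely.
- *Regression to the mean explains the blood results.* Entry is not selected on those values, so the mechanism is weak and indirect there.
- *An inflated effect size will set the later trial's sample size.* The Discussion says only that the data will direct next steps.
- *The blood tests are listed inconsistently.* The Discussion refers to "serial lab values for hemoglobin, hematocrit, vitamin D, iron studies, and AMH", while Quantitative methods names CBC, AMH and vitamin D. The latter list is introduced as examples, so the two do not contradict each other.

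None of this supplies the missing caveat. The word *preliminary* signals imprecision or an early stage; it does not tell the reader that the change may have causes other than the programme.

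**Conclusion.** The concern holds as a matter of attribution. The article attaches the language of impact and benefits to a contrast that has no comparator, and it gives no warning that uncontrolled change cannot be ascribed to the programme. With a background drift of 0.1 to 0.2 SD, 130 to 143 participants and no programme effect, significant improvement would appear roughly 20% to 97% of the time across correlations of 0.5 to 0.8. With 30% loss the range at correlations of 0.5 to 0.7 is 16% to 68%.

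These figures depend on the assumed drift and correlation, since the documents give no SD, treatment rate or cohort calendar. They show that modest drift is enough to mislead. They do not show that such drift will occur, or that any improvement found would be false. If the programme leads participants to seek treatment, part of the treatment-related change is a programme effect, and this design cannot separate that part from usual care. The correction is worth making before results are reported, but it does not call the pilot design into question.

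**What to change.** 1. **Vitamin D.** Replace the raw two-point comparison with a repeated-measures model containing visit, sine and cosine terms for draw date, and a site term. Draw dates normally accompany a laboratory result, so little or no new data collection should be needed. The interval for the visit effect will be somewhat wider. Visit and season can be separated only as far as cohort start dates differ across the year, so the calendar of starts should be reported.
2. **Concurrent care.** Abstract from Epic, already used for screening, the fibroid procedures, hormonal therapy, iron and vitamin D prescriptions, and transfusions between visits. Report them beside the change. Any result for participants with none of these should be labelled descriptive: the group is defined after baseline, and treatment uptake may be a route by which the programme acts. The cost is chart abstraction for 130 to 156 participants. Care received outside the study hospitals may be missed.
3. **Wording.** In Quantitative methods and the Discussion, replace *impact* and *benefits* with *change during the programme*, give changes with confidence intervals, and add one sentence that uncontrolled change cannot be attributed to the programme. The cost is a more modest claim.

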### Survey measures

#### Uterine Fibroid Symptom and Quality of Life (UFS-QOL)

The UFS-QOL is designed to assess symptomology and health-related quality of life for patients managing UF. Scores are calculated on a scale of 0-100, with higher scores indicating a higher reported quality of life [18]. The first 11 questions are framed using a Likert scale (Never; Almost Never; Sometimes; Almost Always; Always) and score from 0-10, with higher scores indicating a better patient experience in the past 6 months. The final 3 questions, reported separately, describe continuity of healthcare after hospitalization, emergency department care, home health care, and social services utilization [19].

#### Everyday discrimination scale

The Everyday Discrimination Scale measures experiences of discrimination in day-to-day life based on racial identity, ancestry and tribal identity, gender and sexuality, income and education, age, religion, ability, and physical appearance including height, weight, and skin tone. Scores range from 0–25, with higher scores indicating more experiences of discrimination [20–22].

#### Patient Health Questionnaire-9 (PHQ-9)

The PHQ-9 screens, diagnoses, and assesses symptom severity for depression over the past 2 weeks on a 4-point Likert scale (Not at all; Several days; More than half the days; Nearly every day), with final scores ranging from 0-27. Major depressive disorder is suggested if 5 or more items are marked as “More than half the days,” and if item 1 or 2 is marked as at least “More than half the days.” Other depressive syndrome is suggested if 2-4 items are marked as at least “More than half the days,” and if item 1 or 2 is checked as at least “More than half the days.” Participants are considered to screen positive for depression if their overall score is 5 or higher [23, 24].

#### Instrument for Evaluation of the Experience of Chronic Patients (IEXPAC)

The IEXPAC survey was developed in the Chronic Care Model theoretical framework [25] and scores participants’ replies to questions about their experience with integrated care for chronic health conditions. IEXPAC focuses on patients’ experiences with entire care teams, and aligns with the Triple Aim framework of improving individual healthcare experience, improving population health, and reducing per capita healthcare expenditures [26]. Overall scores range from 0 (worst experience) to 10 (best experience) [26, 27]. IEXPAC was developed and validated in 2016 to assess patient self-reported experience in the chronic illness context.

### Qualitative methods

#### Methodology and theoretical framework

The qualitative component of this study utilizes methodological triangulation of data: (1) interviews with providers, (2) interviews with patients, and (3) process mapping. Collectively, this formative research will generate comprehensive data needed for improved intervention implementation, scalability, and sustainability.

The Practical, Robust Implementation and Sustainability Model (PRISM) helps facilitate the translation of research into practice by providing a framework for understanding how to promote optimal effectiveness of health services interventions, given the influence of multilevel factors that impact intervention implementation and patient outcomes [22]. PRISM asserts that success of intervention implementation depends on complex interactions between programs, key players, and environments. Specifically, the model details how healthcare interventions influence and are influenced by organizational and patient level factors and how these interactions ultimately impact intervention adoption, implementation, maintenance, reach, and effectiveness (Fig. 1 - Prism Framework) [22]. Based on the PRISM framework, which values and incorporates patient and provider experiences and perspectives, process mapping will be used to comprehensively describe in detail step-by-step patient and provider journeys for CPWF.

#### Individual interviews

Conducting interviews with both patients and providers will be essential for understanding the experiences of each group, which will likely have different perspectives and unique characteristics that will be important to consider for intervention adaptation, implementation, scalability, and sustainability. As such, interviews will be conducted to clarify (a) how patients enroll in CPWF, receive fibroid diagnoses, and engage in educational content and programming regarding treatment options; (b) organizational, cultural, and behavioral barriers and facilitators of engagement in screening and treatment; and (c) areas of possible implementation failure of the education program.

#### Recruitment

Convenience and purposive sampling strategies will be used to recruit 15 patients and 15 providers from each hospital for qualitative interviews. Based on previous work and standards in qualitative research, 15 interviews per demographic is sufficient to obtain thematic data saturation. Additional interviews will be conducted if needed to reach saturation. Eligible providers work at partnering hospitals and actively provide care for patients with UF. Providers will be recruited via email, word of mouth, and participant referral.

Participants in CPWF at partnering hospitals ages 18 to 45, with a new diagnosis of UF, will be eligible to participate. We will recruit patients with UF discovered at the time of: routine office pelvic examinations, exams in the setting of intrauterine device placement requiring bimanual exam and/or ultrasound guidance, and audits of pelvic imaging within the last 12 months done at the study institutions with incidental findings of uterine fibroids. Included participants had pelvic imaging showing at least one fibroid measuring equal or more than two cm and with uterine size less than twenty cm within the last six to twelve months. Targeted recruitment will be conducted through flyers emailed to providers and posted in clinical areas. Self-referral mechanisms are also in place in addition to patient recruitment in clinical waiting rooms and through clinic EHR schedule reviews. Providers who newlydiagnose UF will also refer patients to the study (Fig. 3).

**Fig. 3 Fig3:**
[figure not shown]
Programmatic flow diagram

#### Procedure

All interviews will be conducted in English by a health psychologist with 15 years of expertise in qualitative research and trained research assistants. Informed by the PRISM model, the interview guide will be divided into three sections to reflect data collection goals. Interviews will be recorded, transcribed, verified, and entered into NVivo12, a qualitative data analysis software program, for analysis. Information from the interviews will be used to inform the: (1) process mapping, (2) tailoring of intervention content to address patient and organization specific factors that impact engagement in and implementation of the educational program, (3) creation of activities that directly incorporate aspects of culture to promote engagement in program, and (4) inclusion of culture-specific terminology in materials.

#### Qualitative data analysis

Thematic analysis will be conducted and guided by a five step process outlined by Braun and Clarke to identify key themes that correspond to the theoretical model, PRISM.21 The steps are: (1) Become familiar with the data by reviewing all transcripts, (2) Generate initial codes, (3) Identify themes, (4) Review/revise themes, and (5) Define and name themes. Trained research assistants (RAs) will review each of the transcripts to develop a preliminary coding scheme.

Using NVivo 12, the RAs will code all of the data independently using the preliminary coding scheme as a guide and will create new codes as needed. The RAs will then meet to discuss any coding disagreement until a minimum 90% agreement is achieved. Data analysis will be cyclical and involve continuous development of new codes and constant comparison of themes. To reduce bias, enumeration will be utilized. That is, the frequency of codes applied to transcribed data will be tallied and prevalent codes will be used to form initial thematic categories.

